We will collect health facility level data to assess the overall situation of quality of care from a total of 80 health facilities (40 from intervention health facilities & 40 from control health facilities).From each of the selected health facilities we will collect quantitative data from at least five participants (the chairperson of the health facility governing committee, in charge of the health facility, data focal person , in charge of RMNCAH services and in charge of outpatient services) making a total of 400 participants. This sample is adequate to conduct robust inferential analyses related to the effects of the data use initiative. Moreover, taking p = 50% and applying Cochrane formula while also accounting for refusals and the fact that some health facilities (especially the dispensaries) may not all the five staff, an addition of 10% to the minimum sample will be added to reach 440 participants.Also, from the selected facilities exiting patients will be systematically selected after gender stratification following medical consultations. The exit interview with Client/patients will be approached after they have received the services and are ready to go home. Respondents eligible for interview include all exiting patients or relatives of patients (aged above 18 years). They will be sampled to ensure equal numbers of men and women are captured. The sample is calculated using the Cochran formula (1977) [32]; by taking 50% as a proportion of patients’ perception on quality of primary health care services) and a power of 80% allowing for an estimated error margin of 5%, the sample size obtained was 384 patients. To account for refusals, an additional 10% of the sample will be added (n = 38), making a total of 422 patients.

The qualitative samples and sample sizes for this component are as follows:

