*Sampling and sample sizes*. Our sample for measuring the implementation process (process evaluation) will include implementers of the data use initiative at the council and health facility level. The participants will be implementing partners, health care mangers and health facility governing committee members (CHMT, HFGCs, health facility-in charges and frontline health workers). The fact that all CHMT members are guardians of data use at the council and its respective health facilities, they will all be included in the study (census) thus making a total of 60 CHMT members i.e., at least 15 members from each of the participating council. At least two members of HFGCs will be recruited in the study making a total of 80 HFGC members. A consecutive sample of health care workers from the participating health facilities with a maximum of five participants based on the assumption that the selected facilities should have a minimum of five health care workers, i.e., a total of 200 health workers will be recruited in the study. In addition, routine health facility files and documents will be read and summarized to fit the study context.

*Data collection tools and procedures*. The domains for the implementation process evaluation are reach, adoption, fidelity of implementation, acceptability and sustainability. Data will be collected from the following types of participants and documents; implementing partners, health care managers and health facility governing committee members (CHMT, HFGCs, health facility -in charges and frontline health workers) and health facility documents. Table 1 provides the details on the set of tools and their alignment to objectives and sources of data. In line with our mixed methods design, quantitative data will be gathered using; structured questionnaires, document review/ observation checklists, and semi-structured in-depth interviews (IDIs).

**Table 1 pone.0303552.t001:** The set of tools and their alignment to objectives and sources of data.

Study component	Objective	Domain/ Data required	Sources of data	Data collection tools
Development of a Theory of change	Develop a theory of change (TOC) for data use initiatives and document the process under which such a TOC is developed		Documents, participants (data use initiative designers and implementers)	Document review checklist, Semi structured interview guides for in-depth interview

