Baseline evaluation	Understand the initial (baseline) situation of data use in the study settings in relation to decision making and comprehensive (council or health facility) planning	Socio-demographic characteristics Governance for data use Data use behaviors Equipment and tools for data use Contextual factors for data use	Documents, participants (health facility managers, health care workers, district managers/CHMT members) and members of Health facility governing committees	Document review checklist, Structured questionnaire, semi structured interview guides for in-depth interview
Process evaluation	1) To determine the adoption of data use initiative by the health workers	Uptake of the data use initiative by the implementers (proportion and representativeness of individuals involved in implementing the initiative) [ADOPTION]	Documents, participants (health facility managers, health care workers, district managers/ CHMT members) and members of Health facility governing committees	Document review checklist, structured questionnaire, Semi structured interview guides for in-depth interview
	2) To determine the reach of the data use initiative to health workers at the CHMT and the health facility level	The proportion of health care workers reached by the initiative [REACH]	Documents, participants (health facility managers, health care workers, district managers/ CHMT members) and members of Health facility governing committees	Document review checklist, structured questionnaire, Semi structured interview guides for in-depth interview
	3) To assess the fidelity to data use initiative protocol and SOPs	The extent to which the implementers adhered to the original plan to implement all the essential elements of the program; any deviations or adaptations to the original plan, and follow-up activities [FIDELITY OF IMPLEMENTATION]	Documents, participants (health facility managers, health care workers, district managers/CHMT members) and members of Health facility governing committees	Document review checklist, structured questionnaire, Semi structured interview guides for in-depth interview

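### In facilities with more than five staff, a capped consecutive sample cannot by itself support adoption and reach as proportions, and the article names no other denominator

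*Protocol article*

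**What the plan says.** Table 1 (process evaluation, objective 1) states the aim as "To determine the adoption of data use initiative by the health workers". It measures this as the "proportion and representativeness of individuals involved in implementing the initiative". Objective 2 defines reach as the proportion of health care workers reached. For both objectives Table 1 lists documents and participants as sources, and a document review checklist, a structured questionnaire and interview guides as tools.

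The sampling text for study component 2 opens: "Our sample for measuring the implementation process (process evaluation) will include implementers of the data use initiative at the council and health facility level". At council level all management team members are included, 60 in total. At facility level the rule is "A consecutive sample of health care workers from the participating health facilities with a maximum of five participants". The article supports this cap by assuming that every selected facility employs five or more, and arrives at 200 health workers. At least two governing committee members per facility bring in a further 80. Facility files and documents will also be read and summarised.

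Table 2 gives the process-evaluation document review 20 health facilities and 2 districts.

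**The concern.** A proportion of health workers needs a denominator of all eligible health workers, including those who took no part. Representativeness needs information on the staff outside the group being described. A consecutive sample that stops at five provides neither once a facility employs more than five people. Selection depends on who is present when the team visits, and nothing is recorded about the rest.

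Two things are at stake. First, the adoption and reach figures may be wrong by an unknown amount, upwards if the staff who are present are also the more involved. Second, coverage varies with facility size. If dispensaries and health centres differ in staff numbers, any bias differs between them and could look like a real difference in uptake. The section on implementation processes says that process findings will help to explain variation in effects, so a distortion of this kind could carry over into that interpretation.

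**Working it through.** **Step 1: reproduce the plan's totals.** The sampling text for component 1 gives 40 intervention facilities.
- Health workers: 40 × 5 = 200, as stated. The cap of five is therefore also the working quota.
- Governing committee members: 40 × 2 = 80, as stated.
- Council management teams: 4 × 15 = 60, as stated.

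**Step 2: coverage.** With M staff in a facility, the questionnaire covers 5/M of them: 5/5 = 100%, 5/10 = 50%, 5/20 = 25%, 5/40 = 12.5%. The article gives no value of M beyond an assumed minimum of five. The component 1 text warns that "some health facilities (especially the dispensaries) may not all the five staff", which refers to the five named respondents there. Small facilities, where the problem disappears, are therefore likely to be among those selected. How many larger ones there are is not stated.

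**Step 3: possible size of the bias (illustration only).** Let p be the true proportion involved, and let an involved worker be w times as likely to be enrolled as an uninvolved one. None of M, p or w is in the document. Drawing 5 of M without replacement (3,000 simulated draws per cell) gives these expected sample proportions:

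| M | True p | w = 2 | w = 5 |
|---|---|---|---|
| 10 | 30% | 41% | 52% |
| 10 | 50% | 62% | 76% |
| 10 | 70% | 80% | 90% |
| 20 | 30% | 44% | 63% |
| 20 | 50% | 65% | 81% |
| 20 | 70% | 81% | 91% |
| 40 | 30% | 45% | 66% |
| 40 | 50% | 66% | 82% |
| 40 | 70% | 82% | 92% |

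With w = 1 the expected value equals p. With M = 5 all staff are taken and w has no effect. The excess is about 10 to 16 points for w = 2 and 20 to 36 points for w = 5. As a check, for large M the expectation tends to wp/(wp + 1 − p). At p = 50% this is 1.0/1.5 = 67% for w = 2 and 2.5/3.0 = 83% for w = 5, just above the M = 40 rows. If involved staff were more often away (w below 1), the bias would run downwards.

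**Step 4: would random selection of five be enough?** It removes the bias but leaves each facility's figure imprecise. At M = 20 and p = 50% the standard error is √[(0.25/5) × (15/19)] = √0.0395 = 0.20, or 20 percentage points. The proportion is better taken from the whole list than from five people.

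**Step 5: the document route.** The review could supply a denominator, but the article does not say so. Table 2 gives it 20 facilities and 2 districts, whereas 200/5 = 40 and 80/2 = 40 imply 40 facilities, and 60/15 = 4 implies four councils. The effects column of Table 2 is also half of the text's figure (40 facilities against 80), so this may be a counting slip rather than an intended subsample. As written, the review reaches 20/40 = half of the intervention facilities.

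**The case against.** The strongest reply is that the article does not make the adoption proportion depend on the five respondents alone. Table 1 also names documents and a checklist. The text after Table 1 that lists the health worker questionnaire's content mentions acceptability, fidelity, sustainability and moderators, but neither adoption nor reach. The tools themselves are in a supplementary file that is not shown, and a staff list may be among them. This stands as far as it goes: the absence of a roster from the article does not show that the study lacks one. It does not settle the matter, because the Abstract and Table 1 both tie adoption to the structured questionnaire, and the consecutive selection rule is stated in the article itself.

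A reader might go further and infer that respondents are chosen because they implement the initiative, so that adoption approaches 100% by construction and representativeness cannot be assessed at all. The documents do not support that. The Abstract uses implementers as a role covering health workers and managers, and Table 1 measures uptake among them, so an implementer may or may not have taken the initiative up. The sample is said to include implementers, which is not exclusive. The facility rule draws from health care workers with no involvement criterion.

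The link between presence and involvement is also an assumption. Nor does the article describe a quantitative analysis with facility-level adoption as a moderator, so the effect on explaining heterogeneity is a risk and not a demonstrated failure.

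**Conclusion.** The concern holds in a limited form. In facilities with more than five health workers, the consecutive sample alone cannot give an unbiased adoption or reach proportion, nor show how representative those involved are. Upward bias is plausible but not established, and its size cannot be computed from the document. The figures above rest on assumed staff numbers, true adoption and relative enrolment. The bias is zero with five or fewer staff or where enrolment is unrelated to involvement, and the council-level census is unaffected. The planned document review could close the gap, but the article does not say that it supplies a staff denominator, and its stated coverage conflicts with the sampling text. The point is worth correcting before process fieldwork, because a staff list not taken at the time is hard to reconstruct later.

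**What to change.** Define facility-level adoption and reach with the facility staff list as the denominator. Abstract the list with the document review checklist already planned, in all intervention facilities, and record the cadre and sex of everyone listed so that those involved can be compared with those who are not. Reconcile the 20 facilities in Table 2 with the 40 implied by the sampling text. Where a facility has more than five health workers, select the five questionnaire respondents at random from the list instead of consecutively; with five or fewer, take all of them. The council-level census needs no change.

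The cost is a short abstraction task in each facility, some call-backs for selected staff who are absent, and possibly a lower adoption figure. If the 20 facilities in Table 2 reflect an intended subsample, extending the review to 40 doubles the number of facilities visited for it.

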### 5. Analytical procedures

Descriptive analysis will be used to summarize data where by continuous data will be summarized using mean and standard deviation (SD) as well as medians and interquartile range. Dichotomous variables will be summarized using frequency and percentage. Chi-square test or fisher exact will be used to evaluate bivariate associations between categorical variables where by t-test will be used to estimate association in numeric variables and ascertain whether there mean different between categories. We will also use regression analysis.

Audio-recordings of in-depth interviews and focus group discussions will be transcribed verbatim in Kiswahili guided by a transcription guideline and translated to English. Transcription and translations will be done by the research team that conducted the respective IDIs. Codes will be grouped into categories, sub-themes and themes. Thematic analysis will be used to analyze qualitative data using ATLAS.ti 8 software. Table 2 provides details on data collection tools, administration, sample size and analytical techniques.

**Table 2 pone.0303552.t002:** Data collection tools, administration, sample size and analytical techniques.

S/N	Data collection tool	Level (s) of administration	Method of administration	Sample size (effects measurement)	Sample size (process evaluation)	Analytical techniques
1	Document review checklist	CHMT and Health facility level	physical and e-records, in ODK	Health facilities (N = 40), Districts (N = 4)	Health facilities (N = 20), Districts (N = 2)	Descriptive statistics on frequency, mean and standard deviation, Cross tabulation to compare performance of the participants
2	Semi structured interview guides for in-depth interview	All levels (national, regional, district, health facility, community representatives)	face to face	Patients, dispensary (N = 32), Patients, health center (N = 32), Health care workers, Dispensary (N = 16), Health care workers Health centers (N = 16),	Health facility governing committee members (N = 80), CHMT members (N = 60), RHMT members (N = 4), implementing partners (N = 4)	Thematic analysis will be used to analyze qualitative data using ATLAS.ti 8 software
3	Structured questionnaire	Health facility level	Face to face (guided), in ODK	Health care workers (N = 440), exit patients (N = 422)	Health care workers (N = 200)	Descriptive statistics (mean, standard deviation), Cross tabulation to compare groups’ performance Regression analysis for checking statistical significances among and between the participants Paired sample t test for comparing means between the baseline and end-line surveys
4	DHS2 extraction form	Health facility level / District level	electronic records	Health facilities (N = 40), Districts (N = 4)		Descriptive statistics on frequency, mean and standard deviation, Cross tabulation to compare performance of health facilities/ districts, Paired sample t-test for comparing means between the baseline and end-line surveys

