## Materials and methods

### 1. Study settings

Intervention and comparison districts will be purposively selected from Dar es Salaam & Dodoma and Tanga & Mwanza Regions respectively with a view to minimizing contamination between intervention and comparison arms. In each region, the study area will include 20 health facilities, i.e., 10 health facilities from each district council. Health facility surveys will be conducted at baseline and end line in both the intervention and comparison areas, whereas the data use intervention will reach only the intervention district councils (two districts each in Dar es Salaam (Temeke and Kinondoni) and Dodoma (Dodoma City Council & Chamwino). The intervention districts will also be followed up at 6 months to measure the implementation outcomes and their determinants. To contextualize the settings of this study, we describe the study sites and the program.

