### 2. Study design

This study will adopt an effectiveness-implementation type-2 hybrid design [22] to evaluate the effectiveness of the data use initiatives in improving quality of health service delivery and health outcomes while simultaneously understanding the implementation of the initiatives. Since the data use initiative is implemented in twenty health facilities of two regions, we plan to carry out a before and after controlled design to estimate the combined effects of the data use initiatives in the intervention sites and matched control regions. Simultaneously we plan to assess the implementation processes of the initiatives and this entails the integration of both quantitative and qualitative data collection, analysis, and interpretation methods (i.e. mixed methods) to understand the implementation processes and the influencing factors.

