#### 2) Understand the initial (baseline) situation of data use in the study settings in relation to decision making and comprehensive (council or health facility) planning

To understand the baseline situation, the four councils implementing the data use initiative will be matched equally with comparable councils where the data use interventions will not be implemented. Stratified sampling (to distinguish the level of facilities) will be used in these four councils to select a representative sample of facilities to be observed for one year after the project is implemented. This step combines quantitative and qualitative methodologies to evaluate the current state of data use in the recipient health facilities.

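### The named chi-square, Fisher and t-tests treat respondents as independent, although exposure differs only between four and four councils and respondents are nested in facilities

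*Protocol article*

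**What the plan says.** The study is a non-randomised comparison of areas. Protocol article, section 2 (Study design): "we plan to carry out a before and after controlled design to estimate the combined effects of the data use initiatives". Section 1 (Study settings) says that "the data use intervention will reach only the intervention district councils (two districts each in Dar es Salaam", with the other two in Dodoma. Districts are "purposively selected from Dar es Salaam & Dodoma and Tanga & Mwanza Regions respectively" for the intervention and comparison arms. Section 4, on the baseline situation, adds that "the four councils implementing the data use initiative will be matched equally with comparable councils". On facilities, section 1 states: "In each region, the study area will include 20 health facilities, i.e., 10 health facilities from each district council". That makes eight councils and 80 facilities, 40 per arm.

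Under study component 1, at least five named role-holders per facility give 400 workers, raised to 440. Exit patients come from the same facilities, 384 raised to 422.

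Section 5 (Analytical procedures) states: "Chi-square test or fisher exact will be used to evaluate bivariate associations between categorical variables". T-tests are named for numeric variables, followed by a single sentence saying that regression will also be used. For the structured questionnaires, Table 2 lists cross-tabulation to compare groups, "Regression analysis for checking statistical significances among and between the participants", and paired t-tests between baseline and end line. Clustering, an ICC, a design effect, random effects and robust variance are not mentioned anywhere in the article.

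**The concern.** The named tests take each respondent as an independent observation. Here the exposure is shared by everyone in a council, and many of the outcomes are shared within a facility: availability of drugs and supplies, use of data for planning, and perceived quality of the same service. The five workers are office-holders reporting on the same tools and practices. Their answers can be expected to correlate, as can those of patients leaving the same facility.

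Under any positive correlation of this kind, a between-arm test that counts respondents overstates the information in the data. The stake is a false claim that the initiative improved data use or quality of care, in a study intended to inform scale-up.

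**Working it through.** **Inputs from the article.** 8 councils (4 against 4), 10 facilities per council, 80 facilities; 440 workers and 422 exit patients.

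**Assumptions.** Two-sided 5% level (not stated, but 1.96 reproduces the plan's figure); respondents spread evenly over facilities; 440 and 422 taken as the numbers in the survey round analysed (if they cover both rounds together, clusters are smaller and inflation is less). The article gives no ICC, so a range is shown.

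**Step 1: reproduce the plan's sample sizes.** Cochran for one proportion: n = 1.96² × 0.5 × 0.5 / 0.05² = 384.1, hence 384; adding 38 gives 422. Workers: 80 × 5 = 400; 400 × 1.10 = 440. Both reproduce. The only inflation is 10% for refusals or, for workers, also missing staff, so no design effect is built in.

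**Step 2: formulas.** Design effect DE = 1 + (m − 1) × ICC, with m respondents per cluster. True type I error of a nominal 5% test that ignores clustering = 2 × [1 − Φ(1.96/√DE)]. Example, workers, facility ICC 0.05: m = 440/80 = 5.5; DE = 1 + 4.5 × 0.05 = 1.225; 1.96/√1.225 = 1.77; error 7.7%.

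**Step 3: facility clustering only, end-line between-arm test** (m = 5.5 workers; 422/80 = 5.28 patients).

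| Assumed ICC | DE, workers / patients | Effective n | Type I error |
|---|---|---|---|
| 0.01 | 1.045 / 1.043 | 421 / 405 | 5.5% / 5.5% |
| 0.05 | 1.225 / 1.214 | 359 / 348 | 7.7% / 7.5% |
| 0.10 | 1.450 / 1.427 | 303 / 296 | 10.4% / 10.1% |
| 0.20 | 1.900 / 1.855 | 232 / 227 | 15.5% / 15.0% |

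**Step 4: council clustering only, same test** (m = 440/8 = 55 workers; 422/8 = 52.75 patients).

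| Assumed ICC | DE, workers / patients | Effective n | Type I error |
|---|---|---|---|
| 0.005 | 1.270 / 1.259 | 346 / 335 | 8.2% / 8.1% |
| 0.01 | 1.540 / 1.518 | 286 / 278 | 11.4% / 11.2% |
| 0.02 | 2.080 / 2.035 | 212 / 207 | 17.4% / 16.9% |
| 0.05 | 3.700 / 3.588 | 119 / 118 | 30.8% / 30.1% |

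Correct intervals are wider by √DE: 1.02 to 1.38 times in step 3 and 1.12 to 1.92 times in step 4. With eight councils analysed as unmatched, the multiplier also rises from 1.96 to 2.45 (t on 8 − 2 = 6 df).

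**Step 5: simulation with no true effect** (8 councils × 10 facilities × 5 respondents, 5,000 runs per setting, end-line t-test).

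| Facility ICC | Council ICC | Respondent-level t-test rejects | Council-mean t-test rejects |
|---|---|---|---|
| 0.05 | 0 | 7.0% | 4.9% |
| 0.10 | 0 | 10.7% | 5.2% |
| 0.05 | 0.01 | 13.3% | 4.9% |
| 0.05 | 0.02 | 18.2% | 4.9% |
| 0.10 | 0.05 | 31.2% | 4.9% |

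**Step 6: before-after contrast.** When each cluster's baseline is subtracted from its end line, stable facility and council effects cancel. What remains is the variation between clusters in how they change. The figures in steps 3 to 5 therefore do not carry over to that contrast; its inflation depends on the cluster-by-period variance, for which the article gives no basis.

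**The case against.** The strongest reply is that this is a condensed article. It says that regression will be used, and the form of the model and its variance estimator are commonly left to a fuller document. The chi-square and t-tests are assigned to bivariate associations and are not called the effect estimator. This stands in part: a reader might infer that the regression is known to have no cluster term, and the article does not establish that. But a multilevel regression would not repair the tests that are named, and Table 2 uses cross-tabulation to compare groups and describes regression as a comparison of participants.

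A reader might also infer that every effect estimate in the study is affected in the same way. The article does not support that. DHIS2 indicators and the facility-assessment part of the star rating are measured once per facility, so they have no respondent clustering; only correlation within council or region remains.

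The size is also open. At a facility ICC of 0.01 with no council correlation, the error is 5.5%, which hardly matters. The percentages apply to an end-line between-arm test, whereas the test Table 2 names for change is a baseline to end-line paired t-test. Both points stand and limit the conclusion.

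**Conclusion.** The point holds for respondent-level outcomes compared between arms. The named tests, and the participant-level cross-tabulation and regression as described, ignore nesting in 80 facilities and eight councils, so p-values will be too small and intervals too narrow under any positive ICC. For an end-line test the true error is about 5.5%, 7.6%, 10% and 15% at assumed facility ICCs of 0.01, 0.05, 0.10 and 0.20, and about 8%, 11%, 17% and 30% at assumed council ICCs of 0.005, 0.01, 0.02 and 0.05. The direction does not depend on the assumed values, but the size does. For before-after contrasts the amount cannot be stated without the cluster-by-period variance. Facility-level outcomes are affected only through council or region correlation.

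The facility and council counts differ within the article: section 2 speaks of twenty facilities, and Table 2 of 40 facilities and four districts for effects. These should be reconciled, but they do not alter the conclusion.

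**What to change.** State that effect estimates come from a model with arm, period and arm-by-period terms that accounts for clustering by facility and council (including council-by-period) and for the council matching. Name a small-sample correction suited to the outcome type: for example Kenward-Roger for continuous outcomes, and a bias-corrected GEE or cluster-level summaries for binary ones, since many questionnaire items are yes/no.

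The alternative is to analyse council-level changes with degrees of freedom for few clusters: 8 − 2 = 6 if the matching is ignored, 4 − 1 = 3 if analysed as four pairs. A permutation test is less attractive. Councils were chosen purposively, so it has no randomisation basis, and with four pairs the smallest two-sided p-value is 2/2⁴ = 0.125.

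Keep unadjusted chi-square, Fisher and t-tests for description only. State also that cluster adjustment does not remove confounding of region with arm, because the two arms lie in different regions.

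No new data are needed. The cost is wider intervals and lower apparent power, which matters because the sample sizes contain no design effect.

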To assess the extent of adoption of the data use initiativesTo determine number or proportion of beneficiaries reached by the data use initiativeTo assess the fidelity to data use initiative protocol and SOPsTo assess acceptability of the data use initiative by primary beneficiaries and other stakeholdersTo assess sustainability of the data use initiative in the intervened primary health facilitiesTo determine the implementation challenges and success of the data use initiativesUnderstand the effects of the data use initiative on health system and patient outcomes

To understand the effects of the data use initiative, we will collect data at baseline and end line in order to allow two points measures of the outcome data. In this step, to assess compliance to national and international quality standards, the study team will rely both on the analysis of the routine health information system (at the facility level and district level) and information collected from respondents. Specific research questions include, i) has the quality of primary health facility data improved following implementation of the initiative? ii) What factors have contributed to the observed changes?

Specific objectives:-

Assess the effect/impact of data use initiative on beneficiaries’ capabilities (knowledge, and skills to analyze and interpret data)To evaluate the impact/effect of data use initiative on the quality of data collected in the primary health facilitiesTo determine the impact/effect of the initiative on the use of data for decision making and planningTo evaluate the effect of data use initiative on the performance of primary health facilities in terms of quality of delivered health services (availability drugs, medical supplies and equipment) and client’s satisfaction with the services.

*Study component 1*: *Measuring effects of the data use initiative*. This component aims at establishing the effects of data use initiatives on quality of care and selected health outcomes. To establish and control the counterfactual, data will be collected in the intervention and control councils. This component comprises collection of quantitative and qualitative data at two points (baseline and end line) covering a period of one year.

*Sampling and sample sizes*. This component will collect information from health facility documents , health care workers, and patients. The samples and sample sizes for this quantitative component are as follows

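### For the DHIS2 health outcomes, the only inferential test listed is a within-group paired t-test, which cannot give the controlled before-and-after effect

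*Protocol article*

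**What the plan says.** Section 2 (Study design) states the aim: "we plan to carry out a before and after controlled design to estimate the combined effects of the data use initiatives". Under Study component 1 the reason for the control arm is explicit: "To establish and control the counterfactual, data will be collected in the intervention and control councils". The same component provides for "collection of quantitative and qualitative data at two points (baseline and end line) covering a period of one year", and its sampling text gives "a total of 80 health facilities (40 from intervention health facilities & 40 from control health facilities".

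The analysis is in section 5 and Table 2. Row 4, the DHIS2 extraction form, covers the health outcomes. It lists descriptive statistics, "Cross tabulation to compare performance of health facilities/ districts", and a paired t-test of baseline against end line. The sample size shown there for effects measurement is "Health facilities (N = 40), Districts (N = 4".

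Row 3, the structured questionnaire, lists the same paired test ("Paired sample t test for comparing means between the baseline and end-line surveys"), a cross tabulation between groups, and "Regression analysis for checking statistical significances among and between the participants". The section 5 text adds chi-square or Fisher tests, a t-test between categories, and a one-sentence statement that regression will also be used. No model terms are given.

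**The concern.** In a controlled before-and-after design, the effect is the amount by which the intervention arm changed beyond the control arm. A paired test of baseline against end line asks something else: whether a set of facilities changed at all. For the DHIS2 outcomes it is the only inferential method in the row, so following that row as written leaves the control arm out of the inference on health outcomes.

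The article itself expects change that is not due to the initiative. Its text on data collection tools says that movement in quality of care and health outcomes may come from the initiative or simply from the passage of time. The paired test cannot tell these apart. Run on both arms pooled, it mixes treated and untreated facilities. Run in each arm separately, it invites comparing two p-values in place of estimating a difference.

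**Working it through.** **1. Figures in the plan.** Eight councils with 10 facilities each give 8 × 10 = 80 facilities, 40 per arm. Row 4 shows 40 facilities and 4 districts, which is 80/2 and 8/2. The survey sizes reproduce: 1.96² × 0.5 × 0.5 / 0.05² = 384.2, reported as 384; 384 × 1.10 = 422.4, reported as 422; 80 × 5 = 400 and 400 × 1.10 = 440. These sizes contain no between-arm effect, so the plan has no figure of its own for the contrast at issue.

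**2. What each test estimates.** Let s be the change shared by both arms and e the effect of the initiative.

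- Paired test, intervention arm: s + e
- Paired test, control arm: s
- Paired test, both arms pooled (40 and 40): s + e/2
- Between-arm difference in change: (s + e) − s = e

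Only the last isolates e.

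**3. Size of the problem when e = 0.** The documents give no SD or trend, so s is assumed, as a multiple d of the SD of the facility change score. The paired statistic on n facilities is noncentral t with n − 1 degrees of freedom and noncentrality d√n, tested two-sided at 5%. For n = 40 and d = 0.3 the noncentrality is 0.3 × 6.325 = 1.90, against a critical value of 2.02. The last column is a two-sample t-test on 40 versus 40 independent change scores, from 40,000 simulations.

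| Assumed shared change (SD) | Paired, 40 facilities | Paired, 80 pooled | Between-arm difference in change |
|---|---|---|---|
| 0.1 | 9.5% | 14.3% | 5.0% |
| 0.2 | 23.5% | 42.4% | 5.0% |
| 0.3 | 45.7% | 75.5% | 4.8% |
| 0.5 | 86.9% | 99.3% | 4.9% |

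**4. If each arm is tested separately.** With independent arms, the chance of significance in the intervention arm but not in the control arm is p(1 − p). At 0.3 SD this is 0.457 × 0.543 = 0.248, about 25%. At 0.5 SD it is 0.869 × 0.131 = 0.114, about 11%. It falls because the control arm then usually shows the same change.

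**5. Limit of the 5% figure.** It treats the 80 facilities as independent. They sit in eight councils of 10. If changes within a council correlate with coefficient ρ, the variance of the arm difference is multiplied by 1 + 9ρ, and a test that ignores this exceeds 5%. About 5% is therefore a best case.

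**The case against.** The strongest reply is that Table 2 lists techniques by data collection tool and nowhere calls the paired test the effect analysis. Section 5 names regression without limiting it to a tool, so it could cover DHIS2 data. Row 3 lists regression and a comparison of groups. A condensed article may leave model terms to an analysis plan. The intention to use the controls is clear from the design text, and the Discussion admits residual confounding.

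Much of this stands, and it rules out three stronger readings that a reader might draw.

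- **That the paired test is the plan's sole effect test.** No section says so. For the questionnaires, the complaint is largely that the regression is unspecified.
- **That any common trend will be claimed as an effect.** The documents do not say how results will be read across arms. With separate tests, the misleading pattern drops to about 11% at 0.5 SD.
- **That control facilities are excluded from the DHIS2 analysis because row 4 shows 40.** The Abstract promises extraction from all 80, and the row may be giving a per-arm count. It only fails to show that both arms enter the test.

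The reply does not remove the problem in row 4. That row is not silent: it names one inferential test for the health outcomes, and that test cannot answer the design's question. The general regression sentence makes an arm-by-period model possible but does not state one.

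**Conclusion.** The point holds for the DHIS2 health outcomes: the one inferential test listed in row 4 does not match the controlled design. It extends to row 3 only in part, because the same paired test is listed there beside a regression with no stated arm-by-period term.

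With no true effect, the paired test on 40 facilities would be significant in about 10% to 87% of studies for shared changes of 0.1 to 0.5 SD. Those changes are assumed and illustrate a range; they are not estimates for these facilities. The near-5% rate for the between-arm comparison also depends on independent facilities. The mismatch itself depends on neither assumption, since a paired test has no arm term whatever the trend.

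**What to change.** In section 5 and in Table 2 rows 3 and 4, state that effects are estimated as the between-arm difference in change from baseline and reported with a 95% CI. This can be the arm × period term of a regression, or baseline-adjusted facility change compared between arms. State that all 80 facilities enter, and bring the row 4 counts into line with that. Allow for clustering by facility and by council, using a method suited to a small number of clusters; a facility effect alone does not cover the eight councils. Keep the paired t-test as within-arm description only.

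No new data are needed, because the control facilities are already measured at both times. The cost is a little more analysis work and wider intervals once councils are counted. For example, a council-level comparison has 8 − 2 = 6 degrees of freedom and a t multiplier of 2.45, against 1.99 with 80 − 2 = 78.
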